### Randomization, allocation concealment, and blinding

Participants will be allocated 1:1 to the low- or high-concentration iodine contrast group using a computer-generated allocation protocol prepared by the Department of Preventive Medicine. The allocation sequence will be concealed from the principal investigator, research personnel involved in recruitment and endpoint assessment, participants, image readers, and outcome assessors. The principal investigator and research investigators will not know which contrast concentration is assigned at the time of patient enrollment, image analysis, or endpoint assessment. CT technologists involved in contrast preparation and injection may be aware of the assigned contrast media because the preparations differ; however, they will not participate in patient selection, randomization, image interpretation, endpoint assessment, statistical analysis, or clinical decision-making. After acquisition, CT images will be uploaded to PACS without visible contrast-group identifiers. The principal investigator, research investigators, image readers, and outcome assessors will analyze the anonymized imaging datasets in a blinded arrangement, and the final analytic dataset will be linked to the randomized allocation list only after blinded image analysis is complete. Participants will also not be informed of their assigned contrast concentration. Therefore, the study is described as participant-, investigator-, and reader-blinded, with transparent acknowledgement of technologist unblinding during contrast preparation.

### Contrast media and injection protocols

Participants will receive either high-concentration iodine contrast media (iobitridol 350 mg I/mL; Xenetix 350, Guerbet) or low-concentration iodine contrast media (iohexol 270 mg I/mL; Iobrix 270, Taejoon Pharmaceutical). Dynamic stress CTP will use a fixed volume of 40 mL injected at 5 mL/sec followed by a 30 mL saline chaser in both groups. Therefore, under otherwise identical perfusion-acquisition conditions, the dynamic stress CTP analysis specifically tests whether iodine concentration affects quantitative MBF measurement and interpretability.

CCTA will use a triphasic protocol at 4.5 mL/sec: 0.9 mL/kg of the assigned contrast media, followed by 45 mL of a 70:30 saline-to-contrast mixture (70% saline and 30% contrast medium), and a final 30 mL saline chaser. Two intravenous lines will be secured for contrast media injection and adenosine triphosphate infusion. All injections will be performed with a dual-head power injector (Dual Shot GX7, Nemoto Kyorindo). Weight-based dosing and fixed scan timing are intended to standardize iodine delivery conditions across participants.

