## Discussion

This prospective randomized study protocol addresses a clinically important question in contemporary cardiac CT: whether reduction of iodine concentration in contrast media can maintain CCTA coronary enhancement under standardized acquisition conditions while supporting quantitative dynamic stress CTP assessment. The revised endpoint hierarchy intentionally focuses the trial on contrast media optimization rather than on establishing the intrinsic diagnostic validity of CCTA or dynamic stress CTP.

CCTA is widely used as a first-line noninvasive test for suspected CAD because of its high sensitivity and negative predictive value [16, 20]. However, false-positive findings remain a concern, particularly in patients with heavy coronary calcification, diffuse atherosclerosis, or prior percutaneous coronary intervention [5, 6]. In these settings, distal vessel visualization, side-branch conspicuity, and diagnostic confidence remain important image quality considerations when iodine concentration is reduced.

Dynamic stress CTP provides complementary functional information by enabling quantitative assessment of MBF and ischemia, thereby addressing one of the key limitations of anatomic imaging [7–9]. Although MBF is fundamentally a physiology-derived and model-based parameter, iodine concentration may affect time-attenuation curve amplitude, image noise, arterial input function quality, and segmentation or post-processing robustness. Therefore, assessing MBF comparability under otherwise identical acquisition and injection conditions is justified.

The integration of CCTA and dynamic stress CTP into a single examination offers a comprehensive evaluation of both coronary anatomy and myocardial perfusion. However, this approach increases total iodine exposure, which remains clinically relevant in older patients and in those with chronic kidney disease, diabetes, or cardiovascular comorbidities [10–12]. If low-concentration iodine contrast media maintain coronary enhancement and support quantitative MBF assessment, the protocol may help reduce iodine exposure while preserving the technical basis for integrated anatomic-functional cardiac CT evaluation.

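### The claim that the CTP analysis isolates iodine concentration is unsupported, because each concentration is given as a different contrast molecule

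*Protocol article*

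**What the plan says.** All of this is in the protocol article.

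- **Agents** (Contrast media and injection protocols). One arm receives "high-concentration iodine contrast media (iobitridol 350 mg I/mL; Xenetix 350, Guerbet"; the other receives "low-concentration iodine contrast media (iohexol 270 mg I/mL; Iobrix 270, Taejoon Pharmaceutical".
- **Perfusion injection** (same section). "Dynamic stress CTP will use a fixed volume of 40 mL injected at 5 mL/sec followed by a 30 mL saline chaser in both groups".
- **Inference drawn** (same section). The next sentence opens with a "therefore" and concludes that, "under otherwise identical perfusion-acquisition conditions", "the dynamic stress CTP analysis specifically tests whether iodine concentration affects quantitative MBF measurement and interpretability".
- **Allocation** (Randomization, allocation concealment, and blinding). "Participants will be allocated 1:1 to the low- or high-concentration iodine contrast group". There are two arms with one product each.
- **Model** (Statistical methods). The fixed effects are contrast group, measurement location and, where appropriate, their interaction.
- **Acknowledgement that the products differ** (Randomization, allocation concealment, and blinding). "CT technologists involved in contrast preparation and injection may be aware of the assigned contrast media because the preparations differ". This concerns blinding, not what an effect may be attributed to.
- **Limitations** (Discussion). These cover the single center, the lack of a pilot, clinically driven invasive testing and imaging-only endpoints. The change of molecule is not among them.

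**The concern.** MBF is the key secondary endpoint, and the rationale for measuring it, in the Background and again in the Discussion, is about iodine concentration: its possible influence on attenuation amplitude, noise, the arterial input function and post-processing. The sentence in the contrast section promises that the trial will answer that question specifically. Matching volume, rate, chaser and scanner settings removes those as explanations. It does not remove the change of molecule and formulation, which accompanies the change of concentration in every participant.

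What is at stake is interpretation. MBF has no margin and will be read as quantitative comparability, so much of its value lies in what an observed difference, or similarity, is credited to. If the sentence stands, the results paper can carry a statement about concentration in general when the data compare two named products. A reader who uses another 270 mg I/mL product, or one molecule at two strengths, could be misled about what was tested.

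**Working it through.** The protocol gives no figure on this point. The sample size is set for the primary CCTA endpoint and plays no part here. The check is one of identifiability, followed by a sorting of what is and is not tied to concentration.

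**1. Identifiability.** Inputs: two arms, one product per arm, 129 participants planned per arm (Sample size).

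Let C = 1 for 270 mg I/mL and 0 for 350 mg I/mL. Let M = 1 for iohexol and 0 for iobitridol. Write the expected MBF at a given location as

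E(MBF) = β0 + β1·C + β2·M,

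where β1 is the concentration effect and β2 the molecule or formulation effect.

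| Arm | n | C | M | E(MBF) |
|---|---|---|---|---|
| High (iobitridol 350) | 129 | 0 | 0 | β0 |
| Low (iohexol 270) | 129 | 1 | 1 | β0 + β1 + β2 |

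- C equals M for every participant, so their correlation is 1.0.
- The matrix with columns (1, C, M) has rank 2 of 3.
- The group difference, low minus high, estimates β1 + β2. It equals β1 only if β2 = 0.

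A larger sample narrows the interval around β1 + β2 but does not separate the two terms. Covariate adjustment and the group × location interaction do not help either, because neither adds an arm in which C and M differ. No statistical analysis plan could supply the missing contrast.

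**2. What follows from concentration, and what does not.** Inputs: 40 mL at 5 mL/s for CTP in both arms.

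| Quantity | Formula | 270 arm | 350 arm |
|---|---|---|---|
| Iodine dose, CTP | concentration × 40 / 1000 | 10.8 g | 14.0 g |
| Iodine delivery rate, CTP | concentration × 5 / 1000 | 1.35 g I/s | 1.75 g I/s |

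The relative reduction is the same for both: 1 − 270/350 = 22.9%. Dose and delivery rate are consequences of concentration at fixed volume and rate, so they are part of the concentration effect and raise no separate problem. Molecule and formulation are not consequences of concentration. They are a second difference between the arms.

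**3. The inference against its premises.** The premises are equal volume, rate, chaser and acquisition. The conclusion is a specific test of concentration. The missing premise is that the agent is the same apart from its strength, and the same section shows that it is not.

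**The case against.** Several points on the other side are sound.

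- **The objective is already a comparison of protocols.** Trial design asks whether one contrast protocol is noninferior to the other, and the section on exploratory diagnostic performance states the trial's purpose in the same terms. Randomization answers that question validly. A reader might infer that the aliasing undermines the primary noninferiority test; it does not.
- **The phrase about identical conditions is literally defensible.** "under otherwise identical perfusion-acquisition conditions" refers to acquisition. The Discussion sentence, "assessing MBF comparability under otherwise identical acquisition and injection conditions is justified", refers to acquisition and injection and makes no claim to isolate concentration. A reader might take these as statements that the arms are alike in everything but concentration, but neither phrase covers the agent. The unsupported step is the claim of a specific test.
- **No harm is shown.** Nothing in the documents indicates that the molecule affects MBF, and the mechanisms they name are ascribed to iodine concentration. This stands as a limit on size. It does not make the attribution identifiable.
- **Inference on MBF is already restrained.** No equivalence or noninferiority will be claimed, and a nonsignificant result will not be read as proof of equivalence. That limits what may be concluded from similarity, but it does not address what a difference or similarity is attributed to.
- **The products are named.** Molecule, brand and manufacturer are given, so a careful reader can see the issue. The article nevertheless draws the opposite conclusion from the same facts.

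A reader might also extend the point to safety or heart-rate response. The documents make no concentration-specific claim on either, so there is nothing to correct. The benefit they do claim, lower iodine exposure, follows from concentration at equal volume and does not depend on the molecule.

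**Conclusion.** The statement is wrong as written, not merely brief. The design compares iohexol 270 with iobitridol 350 and does not have the property that the sentence assigns to it. Attribution of an MBF or CTP interpretability result to concentration alone rests on an assumption of no molecule or formulation effect, which the article neither states nor defends.

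The aliasing is complete, but that describes what can be identified; it is not the size of a bias. The documents give no figure for a molecule effect on MBF, and it may be negligible. The conclusion here requires only that such an effect has not been excluded.

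The scope is limited to one sentence about the key secondary endpoint, one missing limitation, and the MBF conclusions that build on them. The randomized comparison of the two protocols, the primary objective and the noninferiority test are unaffected.

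**What to change.** 1. **Contrast media and injection protocols:** replace the claim of a specific test of concentration with a statement that the analysis compares MBF and its interpretability between the iohexol 270 and iobitridol 350 protocols as administered, with injection and acquisition settings matched.
2. **Discussion, limitations:** add that iodine concentration and contrast molecule are confounded by design and cannot be separated within the trial.
3. **Discussion and Conclusions:** word the MBF conclusions as applying to these two products, and make any attribution to concentration explicitly conditional on no molecule or formulation effect.

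No change is needed to the objective in Trial design, the arms, the sample size, the margin or the model. The cost is wording and a narrower claim. It is best made before results are known, so that the qualification cannot look like an explanation after the fact.

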### Patient preparation and stress protocol

Participants will be instructed to abstain from caffeine for 24 h prior to imaging and to withhold theophylline on the day of the examination. In the absence of contraindications, sublingual nitroglycerin will be administered immediately before CCTA to promote coronary vasodilation. For heart rate control, if baseline heart rate is ≥ 60/min, oral ivabradine (5 mg or 7.5 mg) will be administered per protocol. Heart rate will be measured every 10 min for 40 min; scanning will typically commence at approximately 60 min once adequate rate reduction is achieved. Dynamic stress CTP will be performed during intravenous adenosine triphosphate infusion at 140 μg/kg/min for 3 min.

### CT acquisition protocol

All examinations will be performed on a third-generation dual-source CT scanner (SOMATOM Force, Siemens Healthineers) and will comprise coronary calcium scoring, dynamic stress CTP, and CCTA (Fig. 2). For dynamic stress CTP, acquisition will begin 4 s after contrast initiation and proceed in shuttle mode (z-axis coverage 105 mm) over a fixed 32-s interval, yielding approximately 10 to 15 time frames depending on heart rate. Images will be acquired in end-systole using collimation of 96× 0.6 mm and rotation time of 250 ms. Tube voltage will be selected using automatic tube-voltage selection (CARE kV, Siemens Healthineers), and tube current will be modulated using CARE Dose4D (Siemens Healthineers), according to the same institutional cardiac CT protocol in both contrast groups. Physiologic data, including baseline heart rate, peak heart rate during CTP, and heart rate increment, will be recorded prospectively.

**Fig. 2 Fig2:**
[figure not shown]
Integrated anatomic and functional assessment of coronary artery disease using coronary computed tomography angiography (CCTA) and dynamic stress computed tomography perfusion (CTP). After patient preparation and monitoring, noncontrast prospective electrocardiography-guided axial computed tomography (CT) is obtained for calcium scoring. Dynamic stress CTP is acquired in electrocardiography (ECG)-triggered axial shuttle mode during intravenous adenosine triphosphate infusion. CCTA is subsequently performed using prospective ECG-triggered or retrospective ECG-gated scanning based on heart rate. BP, blood pressure; CM, contrast media; HR, heart rate; IV, intravenous

Following completion of dynamic stress CTP, CCTA will be acquired after a standardized inter-exam interval of approximately 10 min. Immediately before CCTA, 0.6 mg sublingual nitroglycerin will be administered. For CCTA timing, bolus tracking will be used with a region of interest placed in the ascending aorta. Scanning will be triggered when attenuation reaches the predefined institutional threshold of 100 HU, followed by a 5-s post-trigger delay. The same bolus-tracking method, trigger threshold, and delay will be applied to both contrast groups. Prospective ECG-triggered axial scanning will be used for heart rate < 65/min, whereas retrospective ECG-gated acquisition with ECG-based tube-current modulation will be used for heart rate ≥ 65/min. The selected tube voltage, CT dose index volume (CTDI_vol_), and dose length product (DLP) will be recorded for each examination.

### CT reconstruction and post-processing

Dynamic stress CTP datasets will be reconstructed in the axial plane (slice thickness 3 mm, 2 mm overlap) using a medium-sharp quantitative kernel (Qr40, Siemens Healthineers) to preserve linearity of iodine attenuation. Post-processing will be performed on a workstation (Syngo.via VB10, Siemens Healthineers) using commercial perfusion software. MBF (milliliters per 100 mL/min) will be derived by parametric deconvolution based on a two-compartment tracer-kinetic model applied to time-attenuation curves. The arterial input function will be placed in the ascending aorta or left ventricular cavity using standardized regions of interest (ROIs). The left ventricle will be segmented according to the American Heart Association (AHA) 17-segment model and polar maps generated for territorial and segmental analyses.

CCTA datasets will be reconstructed with a medium-soft vascular kernel (Bv40, Siemens Healthineers) and iterative reconstruction (ADMIRE strength 3, Siemens Healthineers). Images will be transferred to an offline workstation for post-processing, and optimal phases (mid-diastolic and/or end-systolic) will be selected for evaluation. Dynamic stress CTP and CCTA acquisition parameters, including tube-voltage strategy, ECG-gating approach, reconstruction kernel, slice thickness, and iterative reconstruction settings, will be applied identically in both contrast groups to support reproducibility and minimize confounding by scan parameters.

### Radiation dose assessment

For each examination, CTDI_vol_ and DLP will be recorded for each scan component (calcium scoring, dynamic stress CTP, and CCTA). Effective dose will be estimated as DLP × 0.014 mSv/mGy·cm, and total study dose will be calculated as the sum across components.

### Image analysis

Quantitative CCTA image quality will be evaluated using ROIs in proximal and distal segments of each major coronary artery (left anterior descending coronary artery, left circumflex artery, right coronary artery) to obtain mean attenuation (HU) (Fig. 3A–C). Image noise will be defined as the SD of attenuation in a homogeneous ascending aortic ROI (Fig. 3D). Signal to noise ratio (SNR) and contrast to noise ratio (CNR) will be calculated as SNR = HU_coronary_/SD_aorta_ and CNR = (HU_coronary_ – HU_myocardium_)/SD_aorta_, where HU_myocardium_ is measured from a mid-ventricular septal ROI (Fig. 3E). Measurements will be performed on the optimal phase and averaged for per-vessel and per-patient analyses.

**Fig. 3 Fig3:**
[figure not shown]
Quantitative assessment of coronary computed tomography angiography (CCTA) image quality. **A**–**C** Curved multiplanar reformations of the right coronary artery (RCA), left anterior descending artery (LAD), and left circumflex artery (LCX), showing regions of interest (ROIs) placed in the proximal and distal coronary segments for attenuation measurement. **D** Ascending aortic ROI used for image noise measurement. **E** Septal myocardial ROI used for myocardial attenuation measurement. HU, Hounsfield units

Dynamic stress CTP-derived MBF will be quantified on voxel-wise MBF maps. For segmental analysis, ROIs will be drawn on short-axis MBF maps using the AHA 17-segment model, positioned ≥ 2 mm from endocardial and epicardial borders (Fig. 4). To avoid circularity, MBF thresholds will not be used to define the main MBF analysis set. The main analysis will include all analyzable myocardial segments, with sensitivity analyses in visually nonischemic segments and, when available, territories not supplied by vessels with significant anatomic stenosis or FFR-defined ischemia.

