Recent advances in computed tomography (CT) hardware and software have challenged the traditional linkage between iodine concentration and image quality. In particular, low-tube-voltage techniques augment iodine attenuation and may allow diagnostically adequate enhancement with lower iodine concentration while reducing radiation exposure [13–16]. Previous studies have also demonstrated the feasibility of low-concentration or personalized iodine contrast protocols for CCTA [17–19]. However, the ability of a low-concentration iodine protocol to maintain distal coronary visualization, side-branch conspicuity, overall CCTA diagnostic confidence, and dynamic stress CTP interpretability remains to be determined and is a key motivation for the present randomized protocol. Although dynamic stress CTP-derived MBF is primarily a physiology-based quantitative parameter, contrast iodine concentration may influence attenuation amplitude, image noise, arterial input function quality, time-attenuation curves, and post-processing robustness. Therefore, empirical evaluation of MBF comparability between low- and high-concentration iodine protocols is scientifically justified.

For a contrast media optimization protocol intended for clinical translation, technical image quality assessment alone is not sufficient. It is also important to predefine how downstream invasive coronary angiography (ICA) and fractional flow reserve (FFR) data, when obtained as part of routine care, will be analyzed. In the present study, such invasive reference standard analyses are prespecified as exploratory and hypothesis-generating because invasive testing is clinically indicated rather than mandated by the protocol.

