### Population and setting

The trial plans to enroll 258 adults with known or suspected CAD referred for clinically indicated cardiac CT, including CCTA with planned dynamic stress CTP. Eligible participants will be ≥ 40 years of age, will have electrocardiography (ECG)-gated imaging feasibility, and will have adequate renal function (e.g., estimated glomerular filtration rate [eGFR] ≥ 45 mL/min/1.73 m^2^). Exclusion criteria will include suspected acute myocardial infarction or unstable angina; complex congenital heart disease; significant renal dysfunction or acute kidney injury (e.g., serum creatinine ≥ 1.5 mg/dL or eGFR < 45 mL/min/1.73 m^2^); history of coronary artery bypass grafting (percutaneous coronary intervention/stents permitted and recorded); pregnancy or lactation; history of severe hypersensitivity to iodinated contrast media or vasodilator stress agents; contraindications to nitroglycerin; contraindications to adenosine triphosphate; and uncontrolled arrhythmia precluding diagnostic acquisition. Eligible participants will be recruited from the routine clinical cardiac CT population at our institution during the planned study period.

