### Qualitative image quality assessment

All CCTA and dynamic stress CTP datasets will be independently reviewed by two board-certified cardiovascular radiologists with more than 10 years of experience who are blinded to clinical information and contrast-group assignments. Coronary image quality will be assessed on axial, multiplanar, and curved planar reformation images using a 5-point scale: 5, excellent visualization without relevant artifact; 4, good visualization with minor artifact; 3, adequate visualization with moderate artifact but diagnostic; 2, poor visualization with severe artifact and limited diagnostic confidence; and 1, nondiagnostic image quality. Volume-rendered images will be reviewed as supplementary overview images for global coronary visualization, distal vessel/side-branch conspicuity, and overall diagnostic confidence, but will not be used alone for stenosis assessment. Dynamic stress CTP interpretability will be graded using an analogous 5-point scale. Readers will also record diagnostic acceptability (acceptable vs. nonacceptable) and diagnostic confidence (high, medium, or low). Discrepancies will be resolved by consensus after independent review.

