### Exploratory diagnostic performance analyses: ICA and FFR

Exploratory diagnostic performance analyses will be performed in participants who undergo ICA and/or FFR as part of routine clinical care. The decision to perform CCTA with dynamic stress CTP, as well as subsequent ICA with or without FFR, will be made by the treating cardiologists according to routine clinical care and will not be dictated by study participation. Accordingly, the primary purpose of this trial is to compare contrast media protocols for CCTA enhancement and quantitative dynamic stress CTP assessment, rather than to establish diagnostic validity of CCTA or CTP.

ICA will be interpreted by experienced interventional cardiologists. Anatomic stenosis severity will be recorded per vessel using standard quantitative or visual assessment; ≥ 50% luminal narrowing will define significant stenosis for exploratory CCTA diagnostic performance analyses. For physiology, when FFR is measured, FFR ≤ 0.80 will define functionally significant ischemia in the interrogated vessel. For CCTA diagnostic performance analyses, CCTA-derived stenosis categories will be compared with ICA on a per-vessel and per-patient basis. For dynamic stress CTP diagnostic performance analyses, CTP ischemia (territorial/segmental defects or low MBF) will be compared with vessel-level FFR where available, with mapping of myocardial territories to corresponding coronary vessels using standardized AHA territorial assignments and clinical correlation. Because invasive testing is clinically indicated rather than protocol mandated for all participants, these analyses are subject to potential verification bias and will be interpreted cautiously as prespecified exploratory and hypothesis-generating analyses.

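### The MBF sensitivity subsets are selected after randomization, probably on images that the assigned contrast may affect, so their agreement with the main MBF analysis is weak support for comparability

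*Protocol article*

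**What the plan says.** Under Image analysis, the protocol article fixes the main MBF set: "The main analysis will include all analyzable myocardial segments". It explains the choice: "To avoid circularity, MBF thresholds will not be used to define the main MBF analysis set". The same paragraph then adds two restricted sets: "with sensitivity analyses in visually nonischemic segments and, when available, territories not supplied by vessels with significant anatomic stenosis or FFR-defined ischemia". It does not say on which images, or by what rule, a segment is judged visually nonischemic.

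Four other places bear on this:

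- **Background:** "contrast iodine concentration may influence attenuation amplitude, image noise, arterial input function quality, time-attenuation curves, and post-processing robustness".
- **Qualitative image quality assessment:** the readers are "blinded to clinical information and contrast-group assignments".
- **Exploratory diagnostic performance analyses:** "CTP ischemia (territorial/segmental defects or low MBF) will be compared with vessel-level FFR where available". ICA and FFR are done only when the treating cardiologist asks for them.
- **Statistical methods:** MBF is analyzed with a linear mixed-effects model. There is no margin, no formal equivalence or noninferiority claim, and an explicit statement that nonsignificance will not be taken as proof of equivalence.

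**The concern.** Randomization protects the comparison of all analyzable segments. It does not protect a comparison of segments that were kept because they looked normal on a scan made after allocation. No perfusion imaging other than the stress CTP is described, and that scan is made with the assigned contrast. If the lower concentration reduces measured MBF or degrades the maps, more low-arm segments may be read as abnormal and dropped. The low-arm segments that remain are then the better-perfused ones, and the difference between arms shrinks. Blinding stops readers from acting on knowledge of the arm. It does not stop the image itself from carrying the effect.

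The stenosis/FFR set has a related weakness. FFR exists only where a patient was referred after the scan, and the same may be true of the anatomic data.

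What is at stake is the reading of the key secondary endpoint. With no margin for MBF, a reader will judge comparability from the size of the estimated difference, and may take comfort if a nonischemic subset shows a similar or smaller one. That comfort could be produced by the selection.

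**Working it through.** **Plan's own figure.** There is none to reproduce. The protocol gives no MBF mean, SD, expected difference or share of ischemic segments; its sample size calculation concerns CCTA enhancement only. Every input below is an assumption.

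**Step 1. Hard absolute cutoff.** Suppose MBF is normal and segments below a fixed value are dropped. Let p be the share dropped, a = z(p) and λ = φ(a)/(1 − p). For a small uniform shift between arms, the fraction of the true difference lost is λ(λ − a).

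For p = 0.20: a = −0.842, φ(a) = 0.280, λ = 0.280/0.80 = 0.350, and the loss is 0.350 × (0.350 + 0.842) = 0.417.

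| Share dropped | 8% | 10% | 20% | 30% | 40% | 43% |
|---|---|---|---|---|---|---|
| Loss | 25% | 29% | 42% | 51% | 58% | 60% |

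**Step 2. Slightly blurred cutoff.** Keep a segment with probability Φ((MBF − c)/τ). With s = √(SD² + τ²) and h = (mean − c)/s, the share kept is Φ(h) and the mean of the kept segments is mean + (SD²/s) × φ(h)/Φ(h).

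Take SD 40, c = 100 and τ = 10, with a mean of 130 in the high arm and 110 in the low arm (true difference −20 mL/100 mL/min). Then s = √1700 = 41.23 and SD²/s = 38.81.

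- High arm: h = 30/41.23 = 0.728; kept 77%; mean 130 + 38.81 × 0.3062/0.7666 = 145.5.
- Low arm: h = 10/41.23 = 0.243; kept 60%; mean 110 + 38.81 × 0.3874/0.5958 = 135.2.
- Retained difference: −10.3, about half of −20.

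Over means of 120, 130 and 140, SDs of 30 and 40, shifts of 10 and 20 and cutoffs of 90, 100 and 110, the retained difference is 40% to 78% of the true one. Raising τ to 40 (a much noisier reader) gives 68% to 86%.

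**Step 3. Vary the kind of read.** Steps 1 and 2 assume that the reader applies an absolute level. A simulation relaxed this: 20,000 patients per arm, 16 segments each, random-intercept weighting, intraclass correlation 0.5, 20% ischemic territories with a 1 SD defect, a uniform arm difference of 0.3 SD, and 10% to 40% of high-arm segments excluded.

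| How the reader judges a segment | Loss of the true difference |
|---|---|
| Absolute level, perfect reading | 25% to 59% |
| Absolute level, reader–MBF correlation 0.8 | 15% to 35% |
| Absolute level, correlation 0.5 | 6% to 10% |
| Half relative to the patient's own median (correlation 1 to 0.5) | 3% to 33% |
| Fully relative to the patient's own median | about 0% |

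The exclusion shares show the mechanism. With a perfect absolute read that excludes 20% of high-arm segments, 29% of low-arm segments are excluded. With a fully relative read the shares are equal, at about 20% in each arm.

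**Step 4. Compare with the main analysis.** Keeping all analyzable segments gives no loss from this selection. A criterion that does not depend on the arm also gives about 0%.

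**The case against.** A reader might infer that the plan contradicts its own promise to avoid circularity. The text does not support that. The promise covers MBF thresholds and the main analysis set only, and the main set carries no ischemia restriction.

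A reader might also take a loss of a quarter to 60% as the expected size. That range belongs to a read that acts as a near-exact absolute MBF cutoff. Readers who look for a defect against the patient's remote myocardium would largely cancel a uniform shift, and the loss would be near zero. The protocol does not say which kind of read applies.

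Nor does the protocol state that significant stenosis is judged on the randomized CCTA. The qualification that these data are used when available, together with the definition of stenosis in the paragraph on ICA, fits invasive data at least as well. For that subset the concern is mainly referral, which the protocol already acknowledges as verification bias for its ICA/FFR diagnostic analyses.

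Finally, the MBF inference rests on the mixed model, formal claims are disclaimed, and operational definitions may sit in a fuller document that is not shown. All of this limits the point without removing it. The choice of these subsets is stated in the article, they follow randomization, and blinding does not deal with image-driven selection.

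**Conclusion.** The point holds as a minor one. The all-segment MBF analysis is sound, and no primary conclusion, sample size or decision rule depends on the subsets. But the visual subset, and the stenosis/FFR subset through referral, do not preserve the randomized comparison. Where the read depends at all on absolute MBF, the visual subset is biased toward showing no difference. The possible attenuation runs from about 0% to about 60%, and the position in that range depends mostly on how the visual read is made. Two things are inferred or assumed: that the visual read uses the stress CTP images, and every MBF value used above. If the diagnostic definition of CTP ischemia, which admits low MBF, were reused to select segments, the upper part of the range would become more relevant; the protocol does not say that it will be.

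**What to change.** In Image analysis or Statistical methods:

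1. State that the all-segment analysis governs the MBF conclusion.
2. Label the visually nonischemic and stenosis/FFR subsets descriptive, report the proportion of segments excluded in each arm, and do not cite these subsets as support for comparability.
3. Add, rather than substitute, a sensitivity subset fixed before any contrast is given: participants with a calcium score of zero and no prior PCI or stent. Both items are already collected: "noncontrast prospective electrocardiography-guided axial computed tomography (CT) is obtained for calcium scoring" (Fig. 2 caption) and "percutaneous coronary intervention/stents permitted and recorded" (Population and setting).

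The cost is analysis wording, with no new data or procedures. The added subset will be smaller, its size cannot be predicted from the documents, and a calcium score of zero does not exclude every ischemic segment. It also asks a somewhat different question, about patients with little calcified disease rather than nonischemic myocardium. That is why it should stand beside the existing subsets and not replace them.
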